### Statistical methods

#### Power calculation

To determine the sample size in a design in which two groups are compared at follow-up, controlling for baseline scores, we used the formula n = [2(Z_A_ + Z_B_)^2^ (1 − r^2^)/d^2^] + 1 suggested by Borm [61]. In a longitudinal study by [name] et al. [25], a correlation of. 72 (based on n=137)between depression scores (BDI-II) at baseline and 6 months, as well as a SD of 7.4 at baseline were observed. Therefore, we used *r* = .70 and *SD* = 7.4 as our estimates. The goal of this RCT is to detect an effect size of Cohen’s d = .405 (d = (X_1_ − *X*_2_)/SD) [62] in depression scores between both groups (i.e. (X_1_ − *X*_2_) = d*SD = .405*7.4 = 3). Considering these factors, a minimum of 50 participants is required at t_2_.

The number of participants that need to be recruited per group at baseline is calculated by taking into account the effects of loss to follow-up and non-compliance using the formula n-_b_ = n_e_ (1/p) (1/c^2^ [63, 64]. Based on trial completion rates and compliance rates at 6 months observed in similar trials, we estimate a completion rate of 60 % (i.e. loss to follow-up rate of 40 %) and an 80 % compliance rate [65, 66]. Therefore, we need to recruit 131 participants per group, or 262 total participants at baseline. Recruitment is equally divided between Hamburg and Leipzig, resulting in a number of 66 IG patients and 66 CG patients for Hamburg and 65 patients in each group for Leipzig. The adjustment for non-compliance is conservative as it assumes that non-compliant experimental participants will respond as though they were control participants.

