### Assessment

#### Baseline assessment

The baseline questionnaire (t_0_) is handed to the patient by the research assistant at the end of the face-to-face interview and includes all primary and secondary outcome measures, except for the PHQ-9 depression inventory and the Distress Thermometer, which have been used as screening instruments to assess eligibility prior to the interview, and the GAD-7 anxiety inventory (Table 1).

**Table 1 Tab1:** Study measures

			t_0_	t_1_	t_2_
		Screening/face-to-face interview	(baseline)	(3 months follow-up)	(6 months follow-up)
Demographic characteristics		X			
Medical and treatment-related characteristics		X		X	X
Short Orientation-Memory-Concentration test	(SOMC)	X			
Structured Clinical Interview for DSM Disorders: Major Depressive Disorder Module	(SCID–I)	X			
Distress Thermometer	(DT)	X		X	X
Depression module of the Patient Health Questionnaire	(PHQ–9)	X		X	X
Beck Depression-Inventory II	(BDI–II)			X	X
Generalized Anxiety Disorder Questionnaire	(GAD–7)	X		X	X
Demoralization Scale	(DS)		X	X	X
Brief Fatigue Inventory	(BFI)		X	X	X
Memorial Symptom Assessment Scale Short Form	(MSAS–SF)		X	X	X
Functional Assessment of Chronic Illness Therapy-Spiritual Well-Being Scale	(FACIT–SP)		X	X	X
Death and Dying Distress Scale	(DADDS)		X	X	X
Posttraumatic Growth Inventory	(PTGI)		X	X	X
The Experience in Close Relationships InventoryModified Short Term Version	(ECR–M16)		X	X	X
Quality of Life at the End of Life Cancer	(QUAL–EC)		X	X	X
Couple Communication Scale	(CCS)		X	X	X
Clinical Evaluation Questionnaire			after every therapy session		

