#### Statistical analysis

For the final analyses we will use an intention-to-treat approach (ITT) and compare patients in the assigned treatment groups. Main analyses to evaluate efficacy based on primary (depression) and secondary outcomes at 6 months follow-up (primary endpoint) will be performed using analysis of covariance (ANCOVA). In case of missing outcome data at the primary endpoint, we use the last observation carried forward (LOCF) method. Controlling for baseline test scores as well as demographic and disease-related characteristics, we hypothesize that the mean depression score in the IG will be lower than the one in the CG. Other analyses will include a mixed model approaches (to examine changes over time), regression analyses (controlling for additional factors), and exploratory analyses (of treatment effect modifiers).

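### Table 1 and the text disagree on whether the BDI-II is collected at baseline, while the sample size rests on a BDI-II baseline-to-6-month correlation of .70 and no primary depression scale is named

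*Protocol article*

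**What the plan says.** **Power calculation.** The trial is sized for a comparison at follow-up adjusted for baseline: "we used the formula n = [2(Z_A_ + Z_B_)^2^ (1 − r^2^)/d^2^] + 1". The inputs come from a longitudinal study in which a correlation of .72 "between depression scores (BDI-II) at baseline and 6 months, as well as a SD of 7.4 at baseline were observed". The protocol then states "we used *r* = .70 and *SD* = 7.4 as our estimates". The target is standardized, "The goal of this RCT is to detect an effect size of Cohen’s d = .405", which the protocol equates to 3 points on an SD of 7.4. The result is 50 participants at t2 and, after inflation for loss and non-compliance, 131 per group.

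**Statistical analysis.** The 6-month comparison is an ANCOVA, "Controlling for baseline test scores as well as demographic and disease-related characteristics". Missing values at the primary endpoint are filled by LOCF. The primary outcome is given as depression, with no instrument named. The main study hypotheses also speak only of depression.

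**Baseline assessment and Table 1.** The row for the "Beck Depression-Inventory II" is marked at t1 and t2; its screening and t0 cells are empty. The PHQ-9 is marked at screening, t1 and t2. The text of the same section says that the baseline questionnaire "includes all primary and secondary outcome measures, except for the PHQ-9 depression inventory and the Distress Thermometer", and it adds the GAD-7 to the exceptions. The BDI-II is not among them.

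**The concern.** The three parts of the plan do not fit together. The sample size assumes that 6-month depression is adjusted for a baseline on the same scale and takes that correlation from the BDI-II. The schedule in Table 1 collects no BDI-II before treatment. The sentence introducing the table implies the opposite. The analysis section does not settle it, because it does not say which depression scale is primary.

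This matters because of the factor (1 − r²). At r = .70 it is .51, so the baseline adjustment roughly halves the required sample. If the assumed baseline is not collected, that saving has no support. A centre working from Table 1 would not hand out the form, and a baseline that was missed cannot be recovered later.

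LOCF is affected as well. Under Table 1, a patient lost before t1 has no BDI-II value at all, so the stated method cannot bring that patient into the intention-to-treat analysis of the BDI-II. The protocol expects 40% loss to follow-up by 6 months; how much of it falls before t1 is not given.

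**Working it through.** **Inputs from the power calculation:** r = .70, SD = 7.4, d = .405, completion p = .60, compliance c = .80.

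**Assumption:** the article states neither alpha nor power. Two-sided 5% and 80% power are inferred because they reproduce the stated 50. With the same inputs, one-sided 5% at 80% power gives 40, and two-sided 5% at 90% gives 67.

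**Step 1, reproduce the plan.**
- n = 2(1.960 + 0.842)²(1 − .70²)/.405² + 1 = 49.8, rounded up to 50 per group.
- Recruitment = 50/(.60 × .80²) = 50/.384 = 130.2, rounded up to 131 per group, 262 in total.

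Both figures agree with the protocol. The arithmetic is not at fault.

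**Step 2, vary r and keep everything else.** Power at 50 evaluable per group is approximately Φ(d/√(2(1 − r²)/50) − 1.960). For r = .70 this is .405/√.0204 = 2.836, less 1.960 = .876, giving 81%. For r = .60 it is .405/√.0256 = 2.531, less 1.960 = .571, giving 72%. For r = .50 it is .405/√.0300 = 2.338, less 1.960 = .378, giving 65%.

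| r | n from the plan's formula | Evaluable per group | Recruited per group | Power at 50 per group |
|---|---|---|---|---|
| .70 (plan) | 49.8 | 50 | 131 | 81% |
| .60 (assumed) | 62.3 | 63 | 165 | 72% |
| .50 (assumed) | 72.8 | 73 | 191 | 65% |

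The .60 and .50 rows illustrate adjusting the 6-month BDI-II for the screening PHQ-9. The documents give no correlation for that pair, so these values of r are assumptions.

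**Step 3, the possible readings side by side.**
- *BDI-II primary and collected at t0 (the text is right, Table 1 lacks a mark).* The same-scale ANCOVA can be run, and r = .70 and the sample size stand.
- *BDI-II primary and not collected at t0 (Table 1 is right).* The only depression scale score before treatment is the screening PHQ-9. An ANCOVA can use it, but a same-scale r of .70 is then being applied to a cross-scale adjustment. LOCF has nothing to carry for those lost before t1.
- *PHQ-9 primary.* A same-scale baseline exists from screening. The r, the SD of 7.4 and the 3-point difference come from the BDI-II (range 0 to 63) and are not supported for the PHQ-9 (range 0 to 27).

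**The case against.** The strongest reply is that the text does not except the BDI-II from the baseline booklet, so one omitted mark in Table 1 would explain everything. In that case the planned ANCOVA, r = .70 and the power all hold. This stands as a possibility. The document alone cannot decide it, and the conflict needs resolving either way.

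A second reply is that ANCOVA does not need a baseline on the same scale. This also stands. A reader might infer from Table 1 that the primary analysis cannot be done, or that power falls to the unadjusted level: r = 0 would give about 53% at 50 per group, with 97 evaluable needed. The documents do not support that, since a screening PHQ-9 is available and demographic and disease covariates are planned too.

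A third reply concerns the PHQ-9 as primary outcome. The formula uses only r and the standardized d, so the points and the SD enter only through .405. Nothing shows that the PHQ-9 correlation is below .70, so no loss of power is shown on that reading, only missing support for the inputs.

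Finally, a reader might infer an inflated type I error from two depression scales at t2. No part of the protocol plans to test both as primary, and the analysis section refers to a single mean depression score. The unnamed instrument is a gap, but a false-positive rate cannot be derived from it.

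**Conclusion.** The point holds as an internal conflict with a conditional consequence. Table 1 and the text disagree on the baseline BDI-II, the primary depression instrument is not named, and the sample size depends on a same-scale BDI-II correlation. If Table 1 is what the centres follow, 50 evaluable and 131 recruited per group are unsupported. Power would then depend on an unknown cross-scale correlation, with 72% and 65% as illustrations at r = .60 and .50, against 81% as planned.

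A reader might infer that the trial is underpowered. That is not established. It would require Table 1 to be right and r to be clearly below .70, and the alpha and power behind these figures are inferred from the stated 50.

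**What to change.** 1. **Name one primary instrument.** The BDI-II total score at t2 matches the power calculation, with the PHQ-9 as secondary. If the PHQ-9 is preferred, give an r and a target difference that belong to it.
2. **Reconcile Table 1 with the baseline text.** If the BDI-II is already in the t0 booklet, mark it in the table. If it is not, add it.
3. **If no baseline BDI-II is collected,** state that the screening PHQ-9 is the depression covariate. Restate the power over a declared range of r for that outcome-covariate pair instead of relying on .70. Also say how patients with neither a t1 nor a t2 BDI-II enter the intention-to-treat analysis, since LOCF cannot supply a value for them.

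**Cost.** If the form is already in use, one mark in a table and one sentence naming the outcome. If not, one further 21-item questionnaire at t0, already used at t1 and t2, for patients with advanced disease. If it is not added, the cost is a stated power that may be less favourable than planned.

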#### Statistical analysis

For the final analyses we will use an intention-to-treat approach (ITT) and compare patients in the assigned treatment groups. Main analyses to evaluate efficacy based on primary (depression) and secondary outcomes at 6 months follow-up (primary endpoint) will be performed using analysis of covariance (ANCOVA). In case of missing outcome data at the primary endpoint, we use the last observation carried forward (LOCF) method. Controlling for baseline test scores as well as demographic and disease-related characteristics, we hypothesize that the mean depression score in the IG will be lower than the one in the CG. Other analyses will include a mixed model approaches (to examine changes over time), regression analyses (controlling for additional factors), and exploratory analyses (of treatment effect modifiers).

## Discussion

In the last decades, existential and psychosocial needs of patients in palliative care became increasingly the focus of attention in clinical practice and research. The new World Health Organization (WHO) palliative care resolution ‘Strengthening of palliative care as a component of integrated treatment within the continuum of care’ just recently made clear that palliative care is aimed to be integrated as an essential component of health care systems worldwide [67]. In this resolution the WHO Executive Board explicitly refers to psychosocial and spiritual problems and their treatment. Despite the pronounced necessity for better psychosocial care in palliative treatment, recent studies investigating the effectiveness of psycho-oncological interventions are mostly including patients in earlier stages of the cancer disease. Most RCTs have small sample sizes and compare one active intervention against an inactive control group, no treatment, or care as usual [17].

Our CALM RCT adapted to German cancer care settings addresses the urgent need for developing, optimizing and evaluating manualized psycho-oncologic interventions for advanced cancer patients. To ensure optimal treatment for advanced patients’ specific existential and psychosocial strains it aims to close the gap of treatment options by implementing a short-term, individual and meaning-based intervention.

CALM is already under examination in a RCT in Toronto, Canada, by the research group of [name] who developed CALM. Our RCT is conducted in close cooperation with the Canadian research group, which ensures research quality and helps us to be prepared for possible risks and obstacles during the trial. Currently, studies examining CALM are also conducted in Italy and the United Kingdom, which will lead to a growing international application of the intervention as a psychological dimension of early palliative care. As one of the few psycho-oncological interventions dealing with these issues, our study will contribute important statistical evidence on whether CALM can reduce depression and existential distress in a German sample of advanced and highly distressed cancer patients.

## Abbreviations

CALM: Managing Cancer and Living Meaningfully
CAU: Care as usual
CG: Control group
DT: Distress thermometer
IG: Intervention group
ITT: Intention-to-treat
LOCF: Last observation carried forward
RCT: Randomized controlled trial
SPI: Non-manualized supportive psycho-oncological intervention
